## Abstract

**Background:**

University students are vulnerable to poor mental health, psychological distress, and loneliness relative to nonuniversity student peers. However, the rate of seeking mental health treatment among university students is low. Web-based psychological interventions may provide an opportunity for supporting vulnerable university students who are unlikely to otherwise seek support.

**Objective:**

The aim of this study is to examine the feasibility, acceptability, safety, and efficacy of an existing web-based transdiagnostic cognitive behavioral therapy (CBT) mental health program for use among Australian university students.

**Methods:**

This is a pilot randomized controlled trial comparing a self-directed web-based CBT mental health program with a waitlist control. The self-directed modules will be augmented with optional webchat or telephone coaching with a therapist. The recruitment target is 70 university students who do not present with a clinical mental health disorder. Allocation will be made in a 1:1 ratio and will occur after the initial baseline assessment. Assessments will be completed at baseline, upon completion of a 4-week waitlist (waitlist group only), upon completion of the program, and at 3 months after completion of the program.

**Results:**

The trial was funded in June 2018, and the protocol was approved by the Swinburne University Human Research Ethics Committee in September 2018. Recruitment commenced in October 2018, with the first participant allocated in November 2018. A total of 70 participants were recruited to the trial. The trial recruitment ceased in June 2019, and data collection was finalized in December 2019. We expect the final data analysis to be completed by November 2020 and results to be published early in 2021. The primary outcomes are feasibility, acceptability, safety, and symptoms of depression, anxiety, and stress. The secondary outcomes are psychological wellbeing, quality of life, loneliness, self-reported physical health status, emotion regulation, and cognitive and mindfulness processes.

**Conclusions:**

The acceptability, feasibility, safety, and efficacy of a web-based mental health program in university students will be evaluated. Web-based mental health programs offer the opportunity to engage university students who may be reluctant to seek support through traditional face-to-face mental health services, and the transdiagnostic approach of the program has the potential to address the breadth of mental health concerns of university students.

**Trial Registration:**

Australian New Zealand Clinical Trial Registry ACTRN12618001604291; https://www.anzctr.org.au/Trial/Registration/TrialReview.aspx?ACTRN=12618001604291

**International Registered Report Identifier (IRRID):**

DERR1-10.2196/21307

## Introduction

Young adults aged 16 to 24 years report the highest prevalence of mental health disorders of any age group in the Australian population [1]. University students within this age group are particularly vulnerable to experience poor mental health and psychological distress relative to nonuniversity student peers [2,3]. The most commonly identified mental health issues for university students are depression, anxiety, and stress [4,5]. University students further report unhelpful psychological processes, including negative/critical thinking, self-blame, worry, pessimism, confusion, thoughts of death, loss of confidence, and poor self-esteem [5]. Changes in social relationships specifically may exacerbate the development of mental health symptoms, especially for those who are socially isolated (eg, those living alone or off-campus and those who have migrated for study [3,6,7]). This is consistent with research findings that earlier loneliness predicts more severe depression, social anxiety, and paranoia at a later time [8], and that living away from home for young people may increase their risk of loneliness and poor mental health [9,10].

Despite the high rates of mental health disorders (including anxiety and depression [4,11]) and high psychological distress among university students, the rate of seeking mental health treatment is low [12]. Only about one-third of students who report psychological distress also report accessing on-campus counselling services [13]. According to qualitative reports from university students, stigma related to mental ill health remains a major factor in preventing them from seeking support or treatment for mental health symptoms [5]. Given the reluctance of university students to seek mental health treatment despite high levels of psychological distress, alternate intervention methods to enhance mental health in this population are required. One approach that shows promise to address mental health symptoms and psychological distress for university students is the use of e-mental health or online psychological interventions [14-18]. University students report a willingness to use online mental health resources [19] and perceive multiple benefits of doing so, such as avoidance of stigma, immediacy and ease of access, anonymity and privacy, and greater sense of control over the help-seeking journey [20,21]. Furthermore, students who report being least likely to seek support through an on-campus counselling service or mental health service are most likely to indicate that they would access a web-based student wellbeing program [22]. Thus, online mental health programs and interventions provide a useful approach for supporting vulnerable university students who are unlikely to otherwise seek support.

Uprise (Uprise Services [23]) is an existing web-based mental health program that applies a transdiagnostic cognitive behavioral therapy (CBT) approach for reducing mental health symptoms and improving psychological wellbeing. CBT is considered to be the current gold standard for psychological intervention and has strong evidence for efficacy in reducing symptoms across a range of mental health disorders [24,25]. There is some evidence that CBT-based interventions also influence psychological processes underlying the manifestation of symptoms in many mental health disorders, including correcting habitual thinking errors, reducing biases in attention or memory, and improving emotion regulation [26,27]. The Uprise program comprises a series of self-directed modules that address mindset, values, mindfulness, and stress management. The self-directed modules are augmented with optional telephone or webchat coaching with a trained mental health professional. The option for the self-directed modules to be augmented with coaching support is consistent with results from previous surveys of user preferences indicating that format flexibility is important for the delivery of effective e-mental health interventions [16,28]. Previous trials of similar web-based programs have demonstrated this self-directed CBT-based approach to be effective in reducing symptoms of generalized anxiety, panic disorder, social phobia, obsessive compulsive disorder, and posttraumatic stress disorder in clinically diagnosed adult and student populations [18,29-31]. However, the potential for these interventions to change psychological processes was not examined in these prior studies, and many studies did not present acceptability outcomes.

The primary aim of this trial is to evaluate the acceptability, feasibility, safety, and efficacy of the Uprise program in reducing mental health symptoms among Australian university students. The secondary aims include evaluating the holistic impact of the Uprise program and investigating whether the Uprise program influences psychological processes, such as emotion regulation, cognitive appraisals, and mindfulness. This trial extends on the outcomes of previous trials of similar web-based CBT interventions by examining the broader holistic impact of the intervention rather than focusing only on symptom reduction.

## Methods

### Trial Design

The study will be a pilot randomized waitlist-controlled trial, with two parallel groups, using a 1:1 allocation ratio. Waitlist was selected as the control condition to enable comparison of the Uprise program to students’ usual daily life, while ensuring that all participants had the opportunity to access the Uprise program. Figure 1 presents the study design.

Participants will initially undergo screening for eligibility via telephone interview (T0). Eligible participants will be invited to complete the baseline assessment (T1). Informed consent will be obtained at the baseline assessment. Following the baseline assessment, each consenting participant will be randomized to either the Uprise program or waitlist for the following 4 weeks. Those allocated to the Uprise program will be given access to the program and asked to complete one module per week across the following 4-week period. At the end of the program, these participants will be invited to complete an end-of-treatment assessment (T3). Participants allocated to waitlist will be asked to continue with their usual activities across the following 4-week period, at the end of which they will be invited to complete an end-of-waitlist assessment (T2). Waitlist participants will then be given access to the Uprise program and asked to complete one module per week for the following 4 weeks, at the end of which they will be invited to complete an end-of-treatment assessment (T3). Participants will also be invited to complete a semistructured interview at the end-of-treatment (T3) assessment regarding their experience with the intervention. The interview will be recorded and later transcribed for qualitative analysis. All participants will be invited to complete a follow-up assessment (T4) 3 months after their end-of-treatment (T3) assessment.

The Consolidated Standards of Reporting Trials (CONSORT) flow diagram of the study procedure is shown in Figure 1. The protocol was designed in accordance with the Standard Protocol Items: Recommendations for Interventional Trials (SPIRIT) and good clinical practice (GCP) guidelines (see Multimedia Appendix 1 and Multimedia Appendix 2 for relevant checklists).

**Figure 1 figure1:**
[figure not shown]
Consolidated Standards of Reporting Trials (CONSORT) diagram showing the trial design.

### Study Setting

This trial will be coordinated from Swinburne University of Technology in Melbourne, Australia, and will aim to include students from multiple universities across Australia. Trial assessments will be conducted remotely via telephone and online questionnaires. The trial intervention will also be administered remotely via the Uprise web platform and phone app, with optional coaching calls conducted via either telephone or webchat according to participant preference.

### Sample Size

Seventy participants will be recruited to the trial. Power analysis was conducted using G Power 2.0 for the mental health primary outcome variables (social anxiety and depression), with estimates based on published means and standard deviations and reported effects of similar interventions [32]. The analysis indicated that a minimum of 27 to 45 participants per group would be required to detect moderate changes with 80% power in social anxiety and depression (standardized Cohen *d* of 0.43 to 0.57). Owing to funding constraints, only 35 participants will be recruited to each arm.

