To assess short-term treatment effects, the trajectory of change in each of the outcomes will be examined from baseline (T1) to the end of waitlist (T2) for the waitlist group and from baseline (T1) to the end of treatment (T3) for the intervention group. The trajectory of change in each of the outcomes will be compared between groups. Each analysis will include time (fixed), group (fixed), and the fixed interaction between time and group (time × group) as predictors. A significant time × group interaction effect will indicate a differential rate of change in outcomes between the groups from baseline (T1) to the end of waitlist (T2)/end of treatment (T3).

To assess long-term treatment effects, the trajectory of change in outcomes from baseline (T1) to 3-month follow-up (T4) will be examined in the intervention group only. Sensitivity analysis will also be conducted to determine the trajectory of change from baseline (T1) to 3-month follow-up (T4) in the waitlist group only.

Secondary analyses will include per protocol analysis (only those who complete the four core modules within 6 weeks) and analyses controlling for moderator variables (eg, age, sex, baseline symptom severity, number of Uprise program modules completed, number of coaching calls completed, and number of days accessing the platform). We will report 95% confidence intervals for each test statistic.

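### The stated 27 to 45 per group does not follow from the given effect sizes for a between-arm comparison, so the admitted shortfall at 35 per arm is probably understated

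*Protocol article*

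**What the plan says.** The Sample Size section of the protocol article reports a power analysis for social anxiety and depression. Its result is that "a minimum of 27 to 45 participants per group would be required to detect moderate changes with 80% power in social anxiety and depression", for a standardized Cohen d "of 0.43 to 0.57". The effects come from published means, standard deviations and reported effects of similar interventions. The section names no test, alpha, sidedness, pre-post correlation or dropout allowance. It closes: "Owing to funding constraints, only 35 participants will be recruited to each arm".

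The trial has two parallel arms with 1:1 allocation (Trial Design). Under Planned Data Analysis, short-term efficacy is judged by comparing the arms on change from baseline to the end of waitlist or of treatment: "A significant time × group interaction effect will indicate a differential rate of change in outcomes between the groups". The same section adds: "We will report 95% confidence intervals for each test statistic". Change in mental health symptoms is one of the primary outcomes (Materials), alongside acceptability, feasibility and safety.

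**The concern.** A size quoted per group in a two-arm trial should be the size for comparing the two arms. At d = 0.43 to 0.57 with 80% power, a two-group comparison normally needs about twice the printed numbers.

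The benchmark matters because the planned 35 falls inside the range of 27 to 45. The paragraph then reads as adequate power for the larger effect and a modest gap for the smaller one. Against 50 to 86, 35 is below both ends. What is at stake is how much weight the interaction tests can bear, and whether the printed range is a sound starting point for anyone sizing a later trial.

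**Working it through.** **Inputs from the Sample Size section:** d = 0.57 and 0.43; power 80%; 35 per arm. **Assumed:** two-sided alpha 0.05, in line with the 95% intervals. The pre-post correlation r is not given and is varied.

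**1. Reproducing the printed figures.**
- One-group (paired) test: n = (z₀.₉₇₅ + z₀.₈₀)² / d² = (1.960 + 0.842)² / d² = 7.849 / d². This gives 24.2 (d = 0.57) and 42.4 (d = 0.43). With the noncentral t it is 26.1 and 44.4, rounding up to **27 and 45**. Both ends match exactly.
- 2 × 2 repeated-measures interaction with f = d/2 and r = 0.5: noncentrality λ = 2f²N/(1 − r). The smallest *total* N with 80% power is again **27 and 45**, over both arms together.

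**2. Two-group comparison at the same d.** n per group = 2 × 7.849 / d² = 48.3 and 84.9. With the noncentral t it is 49.3 and 85.9, so **50 and 86 per group**. One-sided 5% would still need 39 and 68.

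**3. Allowing for the pre-post correlation.** If d is on the raw-score SD:
- Change score, which is what a time × group term over two time points tests: effective d = d / √(2(1 − r)). At r = 0.5 this leaves d unchanged, hence 50 and 86. To need 27 at d = 0.57, r must be about 0.73; to need 45 at d = 0.43, about 0.74. At r = 0.741 the sizes are 26.02 and 44.96, which round up to 27 and 45.
- ANCOVA: effective d = d / √(1 − r²). At r = 0.70 the sizes are 25.6 and 44.3, so 26 and 45.

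If d is instead already standardized on the SD of change, r does not enter and the sizes are 50 and 86.

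**4. Power at 35 per arm** (two-sided 5%, noncentral t, no dropout, change score):

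| r | d = 0.43 | d = 0.57 |
|---|---|---|
| 0.3 | 32% | 51% |
| 0.5 | 43% | 65% |
| 0.6 | 51% | 75% |
| 0.7 | 63% | 86% |
| 0.74 | 69% | 90% |
| 0.8 | 80% | 96% |

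ANCOVA gives about 53% and 77% at r = 0.5, and 70% and 91% at r = 0.7. For the change score, 80% power is reached at r of about 0.65 for d = 0.57, but only at about 0.80 for d = 0.43.

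**5. Smallest effect with 80% power at 35 per arm:** d = 0.68 at r = 0.5.

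**6. Side point, dropout.** With an assumed 20% loss (35 × 0.8 = 28 per arm) and r = 0.5, power is 35% and 55%, and the smallest detectable d is 0.76.

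**The case against.** The strongest reply is that the section names no test, so nobody can say from the document which one was used. The exact match with a paired test does not settle it: a between-arm change-score calculation at r = 0.741 yields the same two integers. The source of the effects is not available here. This stands. A reader might infer that the authors sized the trial for the wrong test; the document supports only that the figures cannot be reproduced from what it states.

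A second reply is that any single power figure depends on r. This also stands. A reader might take 43% to 65% as the trial's power, but that is the r = 0.5 row. At r = 0.7 power for d = 0.57 exceeds 80%.

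A third is that the shortfall is disclosed, so readers are not told that the trial has 80% power throughout. That is right as far as it goes. But the disclosure sets 35 against 45, and that benchmark is what is in doubt.

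A fourth is that this is a pilot, with acceptability, feasibility and safety evaluated descriptively and 95% intervals already promised. Those outcomes are indeed unaffected. Nor does the article say that a non-significant interaction will be read as no effect, or that 27 to 45 will size a later trial; both are risks of misreading, not plans. Efficacy is still a primary outcome tested by the interaction, so its stated size should be right.

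Finally, a condensed article may leave the attrition allowance and achieved power to a fuller document. Their absence is not the point here; the printed per-group number is.

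**Conclusion.** The point holds in limited form. As a per-group size for the between-arm comparison, 27 to 45 does not follow from d = 0.43 to 0.57 and 80% power. The standard figures at two-sided 5% are 50 to 86 per group, roughly 1.9 times as many (50/27 and 86/45), and a one-sided test does not close the gap. The printed range can be right only with a pre-post correlation of about 0.73 to 0.74 (change score) or about 0.7 (ANCOVA), which the article does not state.

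The shortfall at 35 per arm is therefore probably, not certainly, understated. Over r = 0.3 to 0.7, change-score power runs from 32% to 63% at d = 0.43 and from 51% to 86% at d = 0.57. Even if r of 0.73 to 0.74 was used, power at d = 0.43 is only about 67% to 69%. These figures assume two-sided 5%, complete data and, where r enters, d on the raw-score SD. The arithmetic is firm; the paired-test origin is an inference.

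**What to change.** Rewrite the Sample Size paragraph to:

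- name the test, alpha, sidedness and any assumed correlation, and say which SD the d values refer to;
- restate the requirement for the between-arm contrast: 50 to 86 per group at r = 0.5;
- give power at 35 per arm over a range of correlations, for d = 0.43 and 0.57: 32% and 51% at r = 0.3, 43% and 65% at r = 0.5, 63% and 86% at r = 0.7; and give the smallest effect detectable with 80% power, about d = 0.68 at r = 0.5;
- if a correlation near 0.73 was used, state and justify it, and still report that power at d = 0.43 is below 80%.

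In Planned Data Analysis, add that efficacy results are presented as estimates with the 95% intervals already planned, and that a non-significant interaction is not evidence of no effect. If dropout is mentioned, label any rate as an assumption.

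The cost is wording only. Recruitment had closed at 70 participants and the final analysis was still pending when the article was written (Results), so no design or model changes. The stated power becomes less favourable unless a high correlation can be justified.

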### Recruitment and Enrolment

Participants will be recruited from Australian universities via social media advertisements, flyers, and student newsletter articles. At Swinburne University, students who are identified as being “at risk” of dropping out of the university owing to mental health concerns will also be emailed and invited to participate in the study. Identification of “at risk” students will be completed by Swinburne University student wellbeing officers according to whether a student did not receive a passing grade for one or more subjects in the previous semester. Student names and email addresses will be shared with the researchers for the purpose of targeted trial recruitment. No other details will be shared with the research team. This targeted recruitment approach has been included to reach vulnerable students who may not have otherwise been motivated to engage in a research study, as well as to emulate potential pathways to accessing the Uprise program if it were to be rolled out as a wellbeing program at universities.

Participants will be invited to register their interest in the study via direct email to the research team or by registering their interest on the study landing page. Some participants may directly comment on social media posts, in which case we will direct them to email the research team or visit the trial landing page. The research team will then email potential participants an information sheet and informed consent form. Once participants have provided their contact details and a preferred contact time, researchers will telephone participants to conduct eligibility screening. The study sponsors will not have access to any identifiable recruitment information.

### Eligibility Criteria

Participants meeting the following criteria will be eligible for the study: (1) aged 17 to 26 years; (2) currently enrolled as a student at an Australian university; (3) competent in English reading and comprehension; and (4) able to receive phone or video conference calls or visit the research center for assessments. The exclusion criteria are as follows: (1) self-reported acute or distressing clinical psychiatric symptoms in the past month (ie, symptoms that the individual reported experiencing as distressing or interfering with their usual daily activities); (2) psychiatric hospitalization in the past month; (3) self-report of any level of suicidality risk; (4) self-report of moderate or severe levels of distress (score equal to or more than 25 on the Kessler Psychological Distress Scale) during screening assessment; (5) self-report of any level of risk of harm to others; and (6) self-report of any level of risk of damage to objects or property.

Participants who report mental health symptoms of a severity that deems them ineligible for the trial will be referred to appropriate mental health services. This is to ensure that these participants receive the appropriate level of care to address the severity of mental health symptoms, as the Uprise program is not designed to address severe symptoms or suicidality. To ensure equitable access to the trial and to minimize sampling bias, these participants will be given the option to undergo eligibility screening again at a later time and to participate in the trial should they meet criteria at this second screening.

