### Allocation and Blinding

Participants confirmed to be eligible following the screening assessment (T0) will be invited to complete the baseline assessment (T1). Following the baseline assessment, participants will be subject to random allocation to either waitlist or treatment with the Uprise program. Block randomization will be applied in this study with a 1:1 allocation ratio using random block sizes of 4 and 6. The randomization sequence will be generated using the Sealed Envelope online randomization sequence generator [33]. Randomization and allocation of participants will be performed by a member of the trial research team ([name]). Allocation will occur within 7 days of the baseline assessment. Participants will be contacted to notify them of their allocation, with those allocated to the treatment group given instructions to access the Uprise program and those allocated to the waitlist group notified of the date for their next assessment (T2).

All outcome assessments will be completed online by participants. It is not possible to blind participants to their allocation owing to the nature of the trial design. The psychologists who provide “coaching” as part of the Uprise program will be blind to participant allocation.

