**Assessments**									
	Demographic form	No	Yes	No	No	Yes	No	No	
	UCLA-LS3^b^	No	Yes	No	Yes	No	Yes	Yes	
	CES-D^c^	No	Yes	No	Yes	No	Yes	Yes	
	SIAS^d^	No	Yes	No	Yes	No	Yes	Yes	
	DASS-21^e^	No	Yes	No	Yes	No	Yes	Yes	
	PANAS^f^	No	Yes	No	Yes	No	Yes	Yes	
	K10^g^	Yes	No	No	Yes	No	Yes	Yes	
	LSNS-12^h^	No	Yes	No	Yes	No	Yes	Yes	
	ERQ^i^	No	Yes	No	Yes	No	Yes	Yes	
	FFMQ^j^	No	Yes	No	Yes	No	Yes	Yes	
	CBPQ^k^	No	Yes	No	Yes	No	Yes	Yes	
	BCIS^l^	No	Yes	No	Yes	No	Yes	Yes	
	PWB-42^m^	No	Yes	No	Yes	No	Yes	Yes	
	AQoL-8D^n^	No	Yes	No	Yes	No	Yes	Yes	
	PHQ^o^	No	Yes	No	Yes	No	Yes	Yes	
	SF-12^p^	No	Yes	No	Yes	No	Yes	Yes	
	WHO-5^q^	No	No	No	No	Yes	No	No	
	PSS-4^r^	No	No	No	No	Yes	No	No	
	Modified SDS^s^	No	No	No	No	Yes	No	No	
	Acceptability measure	No	No	No	No	Yes	No	No	
	Qualitative interview	No	No	No	No	No	Yes	No	

^a^N/A: not applicable.

^b^UCLA-LS3: UCLA Loneliness Scale Version 3.

^c^CES-D: Centre for Epidemiological Studies-Depression.

^d^SIAS: Social Interaction Anxiety Scale.

^e^DASS-21: Depression, Anxiety, and Stress Scale-21 items.

^f^PANAS: Positive and Negative Affect Schedule-Trait and State versions.

^g^K10: Kessler Scale of Distress-10 items.

^h^LSNS-12: Lubben Social Network Scale-12 items.

^i^ERQ: Emotion Regulation Questionnaire.

^j^FFMQ: Five Facet Mindfulness Questionnaire.

^k^CBPQ: Cognitive Behavioral Processes Questionnaire.

^l^BCIS: Beck Cognitive Insight Scale.

^m^PWB-42: Psychological Well-Being Scale-42 items.

^n^AQoL-8D: Assessment of Quality of Life-8 Dimensions.

^o^PHQ: Physical Health Questionnaire.

^p^SF-12: Short-Form Health Survey-12 items.

^q^WHO-5: World Health Organization-Five Well-Being Index.

^r^PSS-4: Perceived Stress Scale-4 items.

^s^SDS: Sheehan Disability Scale.

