#### Mental Health

Psychological distress will be measured with the Kessler Scale of Distress-10 items (K10 [36]). Depression will be measured with the Centre for Epidemiological Studies-Depression (CES-D [37]) and depression subscale of the Depression Anxiety Stress Scale-21 items (DASS-21 [38]). Anxiety will be measured with the anxiety subscale of the DASS-21, and social anxiety will be measured with the 20-item Social Interaction Anxiety Scale (SIAS [39,40]).

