### Planned Data Analysis

Summary data will be provided to describe the number of participants who registered interest in the trial, the number deemed ineligible for the trial and why, and the number who completed each stage of the trial.

Data will be analyzed on an intention-to-treat basis (ie, including all enrolled participants regardless of whether they completed the trial). Acceptability, feasibility, and safety will be evaluated using descriptive statistics. Qualitative interviews will be analyzed using the six-step approach by Braun and Clarke [55] for qualitative data analysis to identify and develop themes from the data to further inform about the acceptability of the intervention to participants.

Results will be summarized as means and standard deviations (or median and range/percentage and number as appropriate) for both groups at baseline (T0) and for the relevant group at the end of waitlist (T2)/end of treatment (T3) for all outcome measures. For both groups, this will demonstrate their results at baseline and again 4 weeks after baseline.

Additionally, the *t* test and chi-square test will be used to evaluate baseline group differences in all demographic and outcome measures. This will be performed to compare the waitlist and intervention groups, and to compare those who drop out from the trial to those who complete the trial. This will enable identification of potential baseline moderator variables or factors that contribute to attrition that can be included as covariates in subsequent analyses.

Multilevel linear mixed effects modeling (MLM) will be used to assess acute and long-term treatment effects in each of the outcome measures. MLM is a regression-based approach that is robust to missing data and provides a more powerful means of analyzing longitudinal data than the ANOVA family of analyses [56]. MLM is robust to missing data because it does not delete cases list-wise due to missing data, but instead includes all available data points for each participant. Missing data analysis will be conducted to determine whether data are missing completely at random. If it is identified that data are missing not at random, covariates will be added to all models to account for systematic variation related to missingness.

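### The K10 has no T1 measurement; using its truncated T0 screening score as baseline leaves the randomised contrast unbiased but would push the uncontrolled K10 trajectories upward

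*Protocol article*

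**What the plan says.** - **Status of the scale.** Primary Outcomes, Mental Health: "Psychological distress will be measured with the Kessler Scale of Distress-10 items (K10 [36".
- **Schedule.** The K10 row of Table 1 reads "K10^g^ Yes No No Yes No Yes Yes". In column order that is yes at T0, no at T1, and yes at T2, T3 and T4. A neighbouring row, the CES-D, reads "CES-D^c^ No Yes No Yes No Yes Yes": no at T0 and yes at T1.
- **Selection.** Eligibility Criteria excludes for "self-report of moderate or severe levels of distress (score equal to or more than 25 on the Kessler Psychological Distress Scale) during screening assessment". People excluded because of symptom severity may be screened a second time and enter if they then qualify.
- **Mode.** Trial Design: "Participants will initially undergo screening for eligibility via telephone interview (T0". Allocation and Blinding: "All outcome assessments will be completed online by participants".
- **Baseline label.** Planned Data Analysis summarises all outcome measures "for both groups at baseline (T0". The same section then starts both its short-term and long-term models at T1. Trial Design, Allocation and Blinding and Table 1 also call T1 the baseline.
- **Long-term analysis.** Change from baseline to T4 is examined in the intervention group alone, with a sensitivity analysis in the waitlist group alone.

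**The concern.** For the K10, the schedule and the stated models cannot both be followed. Started at T1, the K10 model has no baseline. Started at T0, as the descriptive paragraph suggests, it uses the very score that decided who could enter.

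A score selected for being low tends to be higher when measured again, without any real change. Allowing a second screening strengthens that selection. If the T0 items were asked by telephone and the later ones completed online, a mode difference is added. Where there is no concurrent control, nothing separates these effects from the effect of the program.

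**Working it through.** **Inputs from the protocol.** K10 at T0, T2, T3 and T4 only; enrolled T0 scores of 24 or less; 35 per arm; a randomised T2/T3 comparison; single-arm analyses to T4. The protocol gives no planning figure, mean, SD or retest correlation for the K10, so there is no stated number to reproduce.

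**Assumed inputs (not in the protocol).** Applicant K10 normal with mean μ = 18 to 24, SD σ = 6, and retest correlation r = 0.6 to 0.8. The integer cut is taken at 24.5. The second screening is not modelled.

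**Step 1. Is the table row intact?** The K10 row has the same seven cells as the CES-D row. It differs only in having yes at T0 and no at T1, so there is no sign of a broken row.

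**Step 2. Expected drift from selection.** With b = (24.5 − μ)/σ and λ = φ(b)/Φ(b):
- mean T0 score among those eligible: m = μ − σλ
- expected rise at retest with no true change: (1 − r)(μ − m)

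Middle case, μ = 22 and r = 0.7: b = 2.5/6 = 0.417, m = 18.68, SD among those eligible 4.09. Rise = 0.3 × (22 − 18.68) = 1.00 point.

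| μ (σ = 6) | m | rise, r = 0.8 | rise, r = 0.7 | rise, r = 0.6 |
|---|---|---|---|---|
| 18 | 16.45 | 0.31 | 0.46 | 0.62 |
| 20 | 17.66 | 0.47 | 0.70 | 0.93 |
| 22 | 18.68 | 0.66 | 1.00 | 1.33 |
| 24 | 19.53 | 0.89 | 1.34 | 1.79 |

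The range is 0.31 to 1.79 points. Widening the assumptions to SD 5 to 7 and r 0.5 to 0.9 gives 0.1 to 2.6 points.

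**Step 3. Effect on each planned analysis.** Simulation of the middle case: 35 v 35, 5,000 runs, change from T0, tests at 5%. The mode shift is common to both arms; its size and upward sign are chosen only for illustration.

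| True benefit | Mode shift | Between-arm difference | Between-arm rejection | Intervention-arm change | Within-arm rejection |
|---|---|---|---|---|---|
| 0 | 0 | −0.01 | 4.7% | +1.0 | 25% |
| 0 | +1 | 0.01 | 5.2% | +2.0 | 73% |
| 0 | +2 | 0.00 | 5.0% | +3.0 | 97% |
| 2 | 0 | −2.0 | 45% | −1.0 | 26% |
| 2 | +1 | −2.0 | 46% | 0.0 | 5% |

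The between-arm contrast keeps its nominal error rate and recovers the true effect. The single-arm change does not: a true 2-point benefit appears as 1 point (1.0 − 2.0 = −1.0), or as nothing with a 1-point upward mode shift (1.0 + 1.0 − 2.0 = 0).

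**Step 4. What the randomised comparison loses.** In the middle case, truncation lowers the correlation between screening and later K10 from 0.70 to 0.7 × 4.09 / √(0.49 × 4.09² + 0.51 × 36) = 0.56. The covariate then explains about 0.56² = 31% of follow-up variance among those enrolled, rather than 0.70² = 49%.

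**The case against.** **The controlled comparison is safe.** A reader might infer that a bias is built into a primary efficacy test. The documents do not support that. T0 precedes randomisation, so selection and any mode shift fall alike on both arms, and Step 3 confirms it. This stands fully.

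**The K10's primary status is not clear-cut.** The Abstract and Materials give the primary symptoms as depression, anxiety and stress, without distress, and the power calculation concerns social anxiety and depression. The K10 is primary only by its place under the Primary Outcomes heading. CES-D, SIAS and DASS-21 all have T1 values. This stands and limits the importance of the point.

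**Telephone completion of the K10 at T0 is inferred.** Screening is by telephone, but no sentence says how the K10 items were answered, and Study Setting mentions both telephone and online questionnaires. The mode effect is therefore a possibility of unknown size and direction.

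**Two further inferences go too far.** Applicants may be screened a second time, not repeatedly until they pass. T0 is the only K10 before randomisation, but not the only one before treatment, because waitlist participants complete it at T2 before starting the program.

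**The size rests on assumptions.** It does; at the favourable end of the wider range the drift is negligible. Setting it against the planning effects of 0.43 to 0.57 would also mislead: those concern other scales, and this drift is common to both arms.

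What the objection leaves untouched is the contradiction between Table 1 and the models, and the distortion of the single-arm K10 trajectories.

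**Conclusion.** The concern holds in a limited form. For the K10, the schedule and the analysis text conflict: the model has either no baseline or a baseline truncated by the eligibility rule.

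If T0 is used, the time × group comparison remains valid, with only a weaker baseline covariate. The uncontrolled baseline-to-T4 analyses, in the intervention arm and in the waitlist sensitivity version, would drift upward by about 0.3 to 1.8 points under the stated assumptions (about 1.0 in the middle case). That drift hides benefit rather than creating it. A mode effect may add to it or offset it.

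The contradiction is certain from the text. The size of the drift depends on an applicant distribution and retest correlation that the protocol does not give.

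**What to change.** Data collection ended in December 2019, so a T1 K10 cannot now be added. The article describes the final analysis as still pending, and wording changes are enough:

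1. Analyse the K10 as a between-arm comparison of the T2 score (waitlist) with the T3 score (intervention), with the screening K10 as a covariate and not as a time-zero repeated measure.
2. Do not estimate or interpret single-arm K10 change from T0, in the intervention arm or in the waitlist sensitivity analysis.
3. Reconcile the T0/T1 baseline label with Table 1: T1 for scales measured at T1. A blanket relabelling will not do, because PSS-4, modified SDS and WHO-5 have no T1 entry either and need their own statement.
4. If the K10 was in fact collected at T1, correct Table 1 and use T1 as its baseline; items 1 and 2 then fall away.

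The cost is a few sentences of analysis text and the loss of one uncontrolled trajectory per arm for one scale. No new data are needed.
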